## Abstract

**Background:**

Patients with cancer of the lung or oesophagus, undergoing curative treatment, usually require a thoracotomy and a complex oncological resection. These surgeries carry a risk of major morbidity and mortality, and risk assessment, preoperative optimisation, and enhanced recovery after surgery (ERAS) pathways are modern approaches to optimise outcomes. Pre-operative fitness is an established predictor of postoperative outcome, accordingly, targeting pre-operative fitness through exercise prehabilitation has logical appeal. Exercise prehabilitation is challenging to implement however due to the short opportunity for intervention between diagnosis and surgery. Therefore, individually prescribed, intensive exercise training protocols which convey clinically meaningful improvements in cardiopulmonary fitness over a short period need to be investigated. This project will examine the influence of exercise prehabilitation on physiological outcomes and postoperative recovery and, through evaluation of health economics, the impact of the programme on hospital costs**.**

**Methods:**

The PRE-HIIT Randomised Controlled Trial (RCT) will compare a 2-week high intensity interval training (HIIT) programme to standard preoperative care in a cohort of thoracic and oesophageal patients who are > 2-weeks pre-surgery. A total of 78 participants will be recruited (39 per study arm). The primary outcome is cardiorespiratory fitness. Secondary outcomes include, measures of pulmonary and physical and quality of life. Outcomes will be measured at baseline (T0), and post-intervention (T1). Post-operative morbidity will also be captured. The impact of PRE-HIIT on well-being will be examined qualitatively with focus groups/interviews post-intervention (T1). Participant’s experience of preparation for surgery on the PRE-HIIT trial will also be explored. The healthcare costs associated with the PRE-HITT programme, in particular acute hospital costs, will also be examined.

**Discussion:**

The overall aim of this RCT is to examine the effect of tailored, individually prescribed high intensity interval training aerobic exercise on pre-operative fitness and postoperative recovery for patients undergoing complex surgical resections, and the impact on use of health services.

**Trial registration:**

The study is registered with Clinical Trials.Gov (NCT03978325). Registered on 7th June 2019.

## Background

Cancer prehabilitation is an essential component of the multidisciplinary treatment model that optimises patient outcomes at each step on the continuum of cancer care, from diagnosis to survivorship [1, 2]. Prehabilitation aims to reduce post-treatment morbidity and improve pre-treatment health status to increase treatment options, typically surgical candidacy. With the evolution of multimodal approaches to cancer treatment [3], there are now multiple opportunities for prehabilitation in oncology care.

Attenuating postoperative risk is a key priority of preoperative assessment and enhanced recovery after surgery (ERAS) protocols. In lung and oesophageal cancer, complex surgical resection is the only curative intervention, however these procedures are associated with significant postoperative challenges and have the highest mortality and major morbidity risk compared to other oncologic surgeries. Postoperative pulmonary complications (PPCs), which are among the most serious postoperative morbidity, occur in 15–30% of patients post-oesophagectomy and are the primary cause of postoperative mortality, contributing to 45.5–55% of post-oesophagectomy deaths [4]. Comparably, rates of PPCs following thoracic surgery are 25% [5]. The impact of postoperative complications, particularly PPCs on long-term morbidity and quality of life (QOL) is well documented [6], and leads to significant hospital cost, driven by increased use of critical care facilities, and protracted hospital length of stay (LOS). The median cost of hospitalisation post oesophagectomy is $31,375 (€26,368), however this increases by a further $20,777 (€17,461) with serious postoperative complications [7]. Consequently, interventions aimed at reducing postoperative risk may have significant clinical and economic impact.

Cardiopulmonary fitness is an established indicator of postoperative outcome and surgical candidacy. In intra-abdominal surgery, low cardiopulmonary fitness, characterised by an anaerobic threshold (AT) < 11 ml/kg/min provides the most accurate indicator of postoperative morbidity and hospital LOS [8]. Comparably, peak oxygen consumption (VO2peak) < 10 ml/min/kg is predictive of mortality and serious morbidity following major thoracic operations [9]. While a relatively weak association is reported between cardiopulmonary fitness and oesophagectomy outcome specifically [1, 8], it follows from the robust thoracic and intra-abdominal literature that preoperative fitness is an important determinant of oesophagectomy outcome. Furthermore, as oesophageal cancer management moves towards multimodality [3], the attrition impact of preoperative chemo(radio)therapy leads to considerable physical deconditioning and loss of preoperative fitness thus compromising post-operative outcome [10]. In a multivariate analysis, a 1.0 ml/kg/min increase in fitness reduced the odds of complications following colorectal resection by over 20% (OR 0.77 (95% confidence interval (CI) 0.66–0.89) while an increase of 2.0 ml/kg/min was associated with a 40% reduction (OR 0.6 (95%CI 0.45–0.80) [11]. In intra-abdominal surgery, prehabilitation involving inspiratory muscle training (IMT), aerobic exercise and resistance training reduces the incidence of postoperative complications by 41% (OR 0.59 (95%CI 0.38–0.91), with the strongest impact observed in relation to PPCs specifically [12].

While the evidence in intra-abdominal surgery is encouraging, little is known about exercise prehabilitation for major thoracic operations on the lung or oesophagus. Preliminary results from moderate-to-vigorous intensity aerobic exercise programmes prior to thoracotomy for lung cancer have reported improvements in pre-operative cardiopulmonary fitness, and QOL, however trials are limited by single-armed designs and low participant numbers [13]. Exercise prehabilitation for oesophagectomy has typically prescribed IMT, a form of exercise training which strengthens the inspiratory muscles. While initial results from IMT trials were encouraging, a randomised trial of 246 patients, reported no reduction in pneumonia rates or PPCs following oesophagectomy with IMT [14], highlighting the need to prescribe more intensive exercise training to achieve a higher training stimulus for clinical impact.

High intensity interval training (HIIT) has significant potential as an effective and feasible preoperative intervention [15–17]. HIIT consists of alternating periods of high-intensity aerobic exercise and low-intensity exercise or rest, and stimulates superior improvements in VO2peak compared to continuous moderate-intensity aerobic training [15, 18]. The rationale for its use is to increase training time spent at a high percentage of VO2peak (> 80% VO2peak), thus producing a stronger stimulus for cardiovascular and muscular adaptations. Consequently, HIIT provides the best opportunity to create optimal improvements in fitness within the short timeframe for oncologic resection within the clinical pathway. In oncologic resection, preliminary evidence indicates 12–15 sessions of HIIT significantly improves cardiopulmonary fitness in low-fit older adults undergoing lobectomy [16] and hepatic resection [17], however further evaluation in larger cohorts and in those with highest postoperative risk is required. Pilot research from our group supports the feasibility and preliminary efficacy of the proposed intervention.

The primary aim of this study is to improve pre-operative fitness with high intensity interval training (HIIT). This study will examine the physical and economic implications of a targeted programme of exercise prehabilitation prior to major oncologic resection for oesophageal and lung cancer. The HIIT exercise programme will be considered in the context of standard clinical pathways, involving pre-operative oncological therapy and an enhanced approach to postoperative recovery, and compared to standard care.

## Methods

### Study aims

The primary aim of this work is to examine the effect of a preoperative high intensity interval training programme on cardiorespiratory fitness in patients scheduled for oesophagectomy and major lung resections.

Secondary aims are;
To examine if individually prescribed preoperative exercise training can reduce postoperative complication rates following thoracic oncological resections.To determine if individually prescribed preoperative exercise training can impact post-operative physical recovery following complex thoracic oncological resections.To determine if individually prescribed preoperative exercise training restores preoperative cardiorespiratory fitness to pre-treatment levels in patients treated with preoperative chemo(radio)therapy and surgical resection.To examine if individually prescribed preoperative exercise training can reduce postoperative healthcare costs, in particular acute hospital costs.To qualitatively explore participant’s experience of preparation for surgery on the PRE-HIIT trial.

### Study design

PRE-HIIT will be implemented as a randomised controlled trial with two arms: i) an intervention group offered the 2-week HIIT programme in addition to standard care, and ii) a control group receiving standard survivorship care, which involves standard pre-operative advice and a preoperative moderate intensity exercise programme. Figure 1 depicts the flow of participants through the study. The study will take place in the Wellcome Trust-Health Research Board (HRB) Clinical Research Facility (CRF) at St James’s Hospital (SJH), Dublin. Ethical approval has been sought from the Tallaght University Hospital (TUH)/ SJH Ethics Committee. Any amendment to the protocol which may impact on the conduct of the study will be submitted as an amendment for approval to the ethics committees. The study will be performed according to the Declaration of Helsinki. The study is registered with Clinical Trials.Gov (NCT03978325).

**Fig. 1 Fig1:**
[figure not shown]
The Pre-HIIT Trial

### Study participants

Participant Selection Criteria:

#### Inclusion criteria

Patients who are scheduled for either oesophagectomy (2-stage or 3-stage) or major lung resection for the management of primary oesophageal or lung cancer.Date of surgery ≥2 weeks from baseline (T0) assessmentAbility to provide written informed consentAbsence of significant co-morbidities, including metastatic disease, which may adversely impact postoperative outcomeSuccessful completion of a medically supervised cardiopulmonary exercise testPatients with oesophageal cancer scheduled for multimodal therapy including preoperative chemo(radio)therapy and oesophagectomy will be recruited and tested prior to treatment commencement (Dx).

#### Exclusion criteria

The American Thoracic Society/American College of Chest Physicians (ATS/ACCP) absolute contraindications for exercise testing will be applied [19].

In addition, patients undergoing video assisted lobectomy (VATS) for early lung cancer will be excluded.

### Recruitment and screening

The PRE-HIIT trial will recruit 78 patients. Participants will be recruited from SJH, Dublin, Ireland. Participants will be identified at pre-operative clinics and through institutional databases by their clinical team. Eligibility screening will be completed by the research team at SJH. All participants will require written medical clearance from their treating consultant prior to enrolment. Potentially eligible patients will be informed about the study by a member of the research team (SJH) and will receive a participant information leaflet. Following a reflection period of 24–48 h, a researcher will telephone the patient to confirm their interest in participation. Patients who are willing to participate will be invited to attend the CRF at SJH to provide the research team with written informed consent and for baseline testing.

### Randomisation, allocation, concealment and blinding

Following baseline assessment (T0) and registration, participants will be randomised in a 1:1 ratio to either the PRE-HIIT programme or to the standard survivorship care control group, using a computer-generated randomisation list. Randomisation will be overseen by a co-principle investigator, who will have no direct involvement in implementing the trial.

Allocation order and treatment assignment will be concealed from investigators using sealed envelopes generated based on order of recruitment. Study assessments will be performed by an assessor blinded to treatment allocation. Due to the nature of the PRE-HIIT programme, neither the programme implementation staff nor patients can be blinded to the participants’ randomisation assignment.

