### Statistical analysis

Quantitative data analysis will be performed using R IBM SPSS software, employing statistical best practice. A comparison of patient characteristics at baseline will be carried out for each arm. Summary statistics for continuous variables (means and standard deviations or median and ranges as appropriate) and categorical variables (counts and proportions) will be presented. Graphical summaries (boxplots, case profile plots, labelled scattered plots) will be used to compare the distribution s of each response variable and for patient characteristics between the arms. A linear mixed model will be used to model the longitudinal change in the primary response between the groups, allowing for missing data (under the assumption that data are missing at random) and allowing for within subject correlations in the repeated measures across time. The model will adjust for the baseline response variable and other covariates as necessary.

A qualitative approach will be taken to gather participants’ feedback on how the PRE-HIIT study has impacted on their preparation for surgery. Data collection will take a semi-structured approach individual interviews following the intervention. The discussion guide for the interviews will explore topics such as: the impact of the intervention on health, well-being, and activities of daily living, facilitators and barriers to preoperative exercise, and recommendations for future implementation of the programme. Interviews will be digitally audio-recorded and transcribed verbatim for data analysis. A qualitative descriptive approach [32] will be taken to the analysis, with the aim of providing a substantial description of what the participants said, without drawing deep implications from the data. Braun and Clarke’s 6 stage approach to thematic analysis will be used to analyse all data collected [33]. A team of researchers will analyse all transcripts following an agreed process using nVivo 12 (QSR International, Australia).

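### No stratification by cancer site is named for a trial pooling oesophagectomy and lung resection; the cost is chance imbalance and lost precision, chiefly in the unadjusted hospital-cost comparison

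*Protocol article*

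**What the plan says.** Under Randomisation, allocation, concealment and blinding, the Protocol article states that "participants will be randomised in a 1:1 ratio", "using a computer-generated randomisation list", and that allocation is concealed in "sealed envelopes generated based on order of recruitment". It names no stratum or minimisation factor there or elsewhere.

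The Inclusion criteria admit patients "scheduled for either oesophagectomy (2-stage or 3-stage) or major lung resection". Oesophageal patients due for multimodal therapy are also recruited and tested before that therapy starts. In the Background, the article says of oesophageal cancer that "the attrition impact of preoperative chemo(radio)therapy leads to considerable physical deconditioning and loss of preoperative fitness".

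For the primary analysis, the Statistical analysis section says: "The model will adjust for the baseline response variable and other covariates as necessary". The Hospital resources section reasons that, because patients are randomised, hospital-stay costs can be compared as simple differences with ordinary significance tests. No adjustment for site is named. The abstract gives the size: "A total of 78 participants will be recruited (39 per study arm").

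**The concern.** The two operations reach baseline by different routes. Many oesophageal patients arrive after chemo(radio)therapy that, on the article's account, lowers their fitness. Length of stay and cost may plausibly differ between the operations too, although the article gives no figures by site.

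If site is related to an outcome, a chance difference in site mix between the arms shifts the observed arm difference by

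shift = (gap in site share) × (difference in outcome between sites).

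Site variation that is not modelled also stays in the error term. In a trial of 78, a moderate gap is not rare. It can be prevented almost entirely at allocation, but an analysis plan cannot add stratification once patients are allocated.

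**Working it through.** **The plan's own figure.** The Sample size calculation uses a difference of 1 ml/kg/min, SD of change 1.4, 80% power, 5% significance and a two-sample t-test. Taken as two-sided, the exact noncentral t gives 79.0% power at 31 per arm and 80.3% at 32. The stated 64 (32 per arm) is reproduced.

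**Chance of a site gap.** Inputs: 78 patients and 39 per arm (abstract). The number K at the smaller site is not given; I assume 20-50%, that is K = 16 to 39. If x of these fall in one arm, x is hypergeometric(78, K, 39) and

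gap = |x − (K − x)| / 39 = |2x − K| / 39.

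SD of gap = √[K(78 − K)/77] / 39. For K = 39 this is √19.75/39 = 11.4 points; for K = 16, √12.88/39 = 9.2 points.

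A 10-point gap is 3.9 patients and a 20-point gap is 7.8. Because |2x − K| has the parity of K, an even K needs a difference of at least 4 (or 8) patients and an odd K at least 5 (or 9). The probabilities therefore alternate between adjacent values of K.

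| K | ≥10 points | ≥15 points | ≥20 points |
|---|---|---|---|
| 39 | 36.5% | 17.4% | 6.9% |
| 30 | 48.5% | 24.4% | 10.3% |
| 26 | 47.2% | 23.0% | 9.2% |
| 23 | 32.1% | 13.5% | 4.6% |
| 16 | 40.1% | 16.0% | 4.7% |
| all K from 16 to 39 | 27-50% | 10-26% | 3-11% |

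These assume exactly 39 per arm. Simple randomisation without that restriction, simulated at K = 39, gives 43%, 21% and 9%.

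**Complications.** The Background gives pulmonary complication rates of 15-30% after oesophagectomy and 25% after thoracic surgery. The largest difference these allow is 25 − 15 = 10 points. A 20-point gap shifts the arm difference by at most 0.20 × 10 = 2 points.

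**VO2peak change.** The article gives no difference between sites, so this is illustration only. Assume 0.5, 1 or 2 ml/kg/min. A 20-point gap then shifts the arm difference by 0.1, 0.2 or 0.4, against a target of 1. With 32 per arm the standard error is 1.4 × √(2/32) = 0.35. The type I error conditional on that gap, without site adjustment, is about 6%, 9% or 21% (normal approximation). Averaged over all allocations it stays at 5%.

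**Precision.** Under the same assumed differences and an equal split, removing site leaves a residual SD of √(1.4² − d²/4), which is 1.38, 1.31 or 0.98. Power at 32 per arm rises from 80.3% to 81.6%, 85.3% or 98.0%.

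**Stay and cost.** The Background gives a hospital cost for oesophagectomy only, and no stay by site. The shift cannot be computed.

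**After stratification.** With blocks of at most 4 within each site, the arms differ by at most 2 patients per site. The gap is then at most 2/39, about 5 points.

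**The case against.** The strongest reply is that the article never says the list is unstratified. That is inferred from one list, envelopes in recruitment order and no named factor. A journal article may leave strata and blocks to the full protocol, and envelopes in recruitment order do not exclude one series per site. This stands as a caution: the point concerns the scheme as described.

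A reader might infer that the treatment estimate is biased. It is not: 1:1 randomisation without strata is unbiased on average, the overall type I error holds, and leaving 78 patients at one centre unstratified is defensible.

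A reader might also take the open covariate wording as licence to choose covariates after seeing the data. The article does not support that. A covariate list commonly belongs in the analysis plan, which is not shown, and the wording permits adjustment for site.

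On the primary outcome, deconditioning before T0 is mainly a difference in level, which baseline adjustment addresses. The article shows no site difference in T0-T1 change, and it expects no change in controls. It also calls the pulmonary complication rates of the two operations comparable.

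For cost, the Hospital resources section does take surgery type into account when extracting costs. The comparison it then describes is still a plain one, resting on randomisation alone. That, and the low price of stratifying, survive the objections.

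**Conclusion.** The concern holds as a design improvement and not as an error that invalidates the trial. As described, allocation does not control site mix. Gaps of 10 points or more would arise in roughly a quarter to a half of allocations, and gaps of 20 points or more in about 3-11%. This rests on equal arms and an assumed 20-50% of patients at the smaller site.

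The consequence is chance imbalance and lost precision. It is small for pulmonary complications on the article's own rates. For VO2peak change, stay and cost it depends on site differences that the article does not give, so no number of days or euros can be attached. The cost comparison is the most exposed because it is the one place where the article describes a plain comparison with no adjustment.

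**What to change.** Stratify the computer-generated list by cancer site (oesophagus or lung), with randomly varying block sizes and one envelope series per site. Include site as a covariate in the primary linear mixed model and in the length-of-stay and cost comparisons, replacing the unadjusted cost test under Hospital resources with a site-adjusted difference. If the full protocol already stratifies by site, say so in the article and carry the factor into these analyses.

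The cost is a second envelope series at a single centre and one degree of freedom per model. Site is known before allocation, and the sample size does not change. The Study status section places the start of recruitment in the future, so the list could be regenerated. If patients have already been allocated, keep the existing list and fix the site covariate before outcome data by arm are seen.

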### Intervention

#### Preoperative exercise intervention

The exercise intervention will take the form of a supervised programme, completed for at least 2 weeks, up to 5 days per week preoperatively. The feasibility of this protocol has been established by our PHIIT trial, which recruited patients scheduled for thoracotomy and colorectal surgery at St James’s Hospital, with compliance rates of 86% and adherence of 98%. Furthermore, the study design is similar to the format prescribed by the PREPARE trial [20], which specified a minimum study duration (at least 2 weeks) but continued to prehabilitate patients for longer in the lead up to surgery to optimise the benefits gained [21]. The 2-week preoperative timeline was found to be acceptable in the oesophagectomy clinical pathway at our Centre.

The HIIT programme will be performed on an electromagnetically braked cycle ergometer in the exercise physiology room at the CRF in St. James’s Hospital under the supervision of a physiotherapist with experience in exercise prescription and exercise oncology. Exercise sessions will be individually supervised and scheduled at a time of convenience for each participant. Each exercise session will last 40 min and will include warm-up, exercise training and cool-down components. Lactate threshold, measured during the baseline CPET, will be used to determine the exercise intensity.

The intervention will prescribe the same HIIT protocol used by the PHIIT trial, with established safety and feasibility. The training protocol will prescribe 15 s intervals of exercise and passive recovery. The highest resistance reached during the baseline CPET (measured in watts) will be recorded as the peak power output (PPO). During training, participants will undergo a 5-min warm-up at 50% PPO, followed by up to 30 min of HIIT with intervals of 15 s at 100% PPO with 15 s recovery periods at 0 watts. Vital signs including heart rate, blood pressure, perceived exertion, and oxygen saturation levels will be measured throughout. A 3-min cool down will be performed upon session completion followed by a passive recovery period of up to 7 min. Preliminary evidence from both our PHIIT feasibility trial and the published literature [16, 17], supports the hypothesis that this exercise prescription will produce a clinically and significantly meaningful increase in cardiopulmonary fitness.

